#### Qualitative assessment and economic evaluation

At the end of the study, walk-through surveys will provide direct qualitative assessment of any changes in safety provisions during the trial.

During the course of the study, we will also collect information from mills which receive the intervention on costs of its implementation and any direct or indirect savings that may have resulted. We will also document changes in staff turnover, sickness absenteeism and associated costs. Finally, if the intervention proves to be successful we will undertake a simple cost-effectiveness analysis to inform its delivery and value at a broader level.

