Engineering controls are the most effective way of reducing dust levels, but are relatively costly. Where they cannot be afforded, standard respirators (N95 and others) are recommended for cotton mill workers [18], but access to them has been limited in developing countries such as Pakistan. While there is little direct evidence regarding the effectiveness of such respirators and face-masks for protection against specific hazards [19], it is likely that they will provide some protection. In addition, training in occupational health and safety (OHS) may be beneficial, although the effectiveness of different learning approaches in such training is unknown [18, 20]. Thus, where engineering controls are not practicable, the best opportunity for the prevention of byssinosis may lie in a combination of various training methods with appropriate administrative controls and provision of face-masks. However, there is first a need for robust epidemiological assessment of such interventions, including through trials [20]. Few trials have been undertaken to test interventions to reduce occupational exposures; recent work by Basinas et al., for example, has shown that education and exposure feedback can reduce dust exposures of farmers by about 25% [21].

Building on an earlier pilot investigation [22], the study described in this paper is a randomized trial to assess the effectiveness of a multifaceted intervention package in reducing dust levels in the spinning and weaving sections of textile mills, decreasing the prevalence of respiratory symptoms associated with cotton-dust exposure among textile workers, and improving their lung function. As a secondary objective, it also aims to determine the effectiveness of the intervention package in reducing sickness absence attributed to respiratory disease.

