### Measurements and their frequencies

To assess the impact of the intervention, surveys will be carried out across all mills at baseline (i.e., before the intervention is implemented), and then at follow-up 3, 12 and 18 months later (Figs. 2, 3 and 4, and Additional file 1). The surveys will include detailed interviews using a questionnaire, and spirometry for each worker. In addition, personal dust exposures, measured with Institute of Occupational Medicine (IOM) samplers, will be recorded for selected sub-samples of participants.

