### Statistical analysis

Data will be entered through Epi Data and analyzed with STATA. Frequency counts will be derived for baseline socio-demographic variables and respiratory symptoms (categorical variables). Measures of central tendency and dispersion will be reported for continuous variables (cotton-dust levels and lung function indices). Correlations between the cotton-dust levels and lung function (FEV_1_, FVC and FEV_1_/FVC ratio) will be assessed through Pearson’s correlation coefficient.

Models based on generalized estimating equations (GEEs) will be developed to determine changes in the cotton-dust levels, frequency of respiratory symptoms, FEV_1_ (lung function indices) and respiratory sickness absenteeism. The changes in these outcome variables from baseline will be compared between the intervention and control groups. The GEE models will take into account the clustering by mills, as well as the correlation between repeated measures. Multicollinearity will be assessed between covariates and will be taken into account in the multivariable models.

We will analyze by intention to treat, and workers will be classified according to their assigned treatment group at the time of randomization. Sensitivity analyses will be performed to explore the potential impact of losses to follow-up.

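### Savings are to be collected only from intervention mills, so as worded they have no concurrent control, and the cost-effectiveness analysis could inherit this

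*Protocol article*

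**What the plan says.** The economic paragraph of the protocol article (Methods/design, Qualitative assessment and economic evaluation) contains three statements:

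- On costs and savings, the team will "collect information from mills which receive the intervention on costs of its implementation and any direct or indirect savings that may have resulted".
- On workforce measures: "We will also document changes in staff turnover, sickness absenteeism and associated costs". This sentence names no arm.
- On use of the data: "if the intervention proves to be successful we will undertake a simple cost-effectiveness analysis".

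Elsewhere, the Background gives a secondary objective: "it also aims to determine the effectiveness of the intervention package in reducing sickness absence attributed to respiratory disease". The Statistical analysis section includes among the outcomes for the generalized estimating equation (GEE) models "frequency of respiratory symptoms, FEV_1_ (lung function indices) and respiratory sickness absenteeism", and continues: "The changes in these outcome variables from baseline will be compared between the intervention and control groups". The section on measurements and their frequencies says that "surveys will be carried out across all mills at baseline", and again at 3, 12 and 18 months.

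**The concern.** The savings sentence treats two quantities alike that need different data. The cost of delivering the package can be observed directly, and only where it is delivered. A saving attributed to the package is a causal quantity, so it needs an estimate of what absence, turnover and costs would have been without it. The trial randomizes 14 mills to supply that comparison, and the sentence leaves them out.

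The document itself gives reasons to expect background change. Its Discussion says that labor turnover is generally high and that control mills may start safety initiatives of their own because they are being observed. The 18-month survey also falls in the opposite half of the year from baseline. With data from one arm, movement from such sources would be credited to the package or charged against it. The cost-effectiveness analysis is meant to inform wider delivery, so an error there could reach policy. Cost and savings data are gathered while the trial runs, and control-mill figures not recorded at the time may not be recoverable later.

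**Working it through.** No figure in the plan bears on this point, so the check compares the sections.

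**1. Which mills does the savings sentence cover?** The Intervention section says control mills get no intervention during the main study. During the trial, mills that receive it are therefore the intervention arm. No section shown provides for savings data from control mills.

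**2. Does the article name both arms when it means both?** Usually. Surveys cover all mills, dust sampling is stated for both arms, and knowledge, attitudes and practices are compared between arms. The savings sentence names one arm, so it reads as a stated limit and not as loose condensation.

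**3. What can each design identify?** Let *t* be the effect of the package on a cost-bearing quantity and *b* the background change over the same period, taken as equal on average in the two arms because of randomization.

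- Change in intervention mills = *t* + *b*
- Change in control mills = *b*
- Between-arm difference in change = (*t* + *b*) − *b* = *t*

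Intervention-mill data alone give *t* + *b*, and no analysis of those data can separate the two terms.

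**4. How far does the limit extend?**

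| Quantity | Economic paragraph | Statistical analysis section |
|---|---|---|
| Implementation cost | Intervention mills only (correct) | Not modelled |
| Savings | Intervention mills only | Not modelled |
| Respiratory sickness absence | Part of sickness absenteeism; no arm named | In the GEE models, change compared between arms |
| Staff turnover | No arm named | Not modelled |
| Associated costs | No arm named | Not modelled |

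The limit is explicit for savings only. For respiratory absence, the planned comparison cannot be carried out without control-arm data, so such data are implied. For turnover and associated costs, the arm is not stated anywhere in the text.

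**5. Size.** The document gives no absence rate, turnover rate or unit cost. As pure illustration, assume 2 days of respiratory absence per worker per year and a background change of 10 to 30%. With *t* = 0, one-arm data would show an apparent change of 0.10 × 2 = 0.2 to 0.30 × 2 = 0.6 days per worker per year. This only restates the assumed inputs and is not an estimate for this trial.

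**The case against.** A reader might infer from the shared paragraph that absenteeism and turnover are also collected only in intervention mills, leaving the sickness-absence objective without control data. The document does not support this. The sentence on those measures is separate and carries no limit, and the Statistical analysis section compares change in respiratory sickness absenteeism between arms. An unrestricted sentence should be read consistently with that plan. The article does not say whether absence comes from interviews or mill records, but an article may leave that detail to the full protocol. The schedule figures and the additional file on measurements, which are not shown, may also settle it.

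A reader might also infer that savings will be computed as an uncontrolled before-after change. The text does not say how savings will be derived. If absence, turnover and associated costs are in fact recorded in both arms, part of the comparator for savings already exists.

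The consequence is also bounded. The article calls the economic evaluation limited, the cost-effectiveness analysis is simple and conditional on success, and none of the four primary outcomes depends on it. The seasonal argument applies to the 18-month survey and not to the one at 12 months.

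All of this stands, and it narrows the point. It does not remove it: the savings sentence still names one arm. If it is followed as written, what remains is each mill's own baseline or its managers' attribution, and neither is a concurrent control.

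**Conclusion.** The point holds for savings. As worded, they are collected without a concurrent control and would mix any effect of the package with background change; the cost-effectiveness analysis could inherit this if it is run. Limiting implementation costs to intervention mills is correct. For turnover and associated costs the fault is an ambiguity about which mills supply the data. For respiratory sickness absence, control-arm data are already implied, and the economic paragraph only needs to say so.

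Neither the direction nor the size of the bias can be derived from the document. The conclusion rests on reading the savings sentence literally and on the expectation that absence, turnover or costs may move over 18 months for reasons other than the package. It does not touch the trial's primary comparisons.

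**What to change.** In the economic paragraph:

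1. Keep implementation costs as intervention-only.
2. State that staff turnover, sickness absenteeism and associated costs are recorded in the same way and over the same calendar periods in all 28 mills, consistent with the Statistical analysis section.
3. Define the savings used in the cost-effectiveness analysis as the between-arm difference in change from baseline.
4. Label any saving reported only by intervention mills as uncontrolled.

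The cost is small: extra data entry at 14 control mills that are already surveyed four times (baseline, 3, 12 and 18 months) and whose Human Resources departments already identify eligible workers. The change should be made while data are still being collected.

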### Study outcomes

The primary outcomes of the trial at 18 months post intervention, will be: (1) personal dust exposure levels (in mg/m^3^), and their change from baseline, in the intervention as compared with the control arm; (2) dust levels in different sections of the mill (in mg/m^3^), and their changes from baseline, in the intervention as compared with the control arm; (3) changes from baseline in the prevalence of respiratory symptoms, in the intervention as compared with the control arm (a composite variable will be used for presence of one or more respiratory symptoms including; cough, sputum, wheeze, shortness of breath and chest tightness) and (4) changes in FEV_1_ from baseline to follow-up, in the intervention as compared with the control arm.

### Process evaluation

Process evaluation will be performed according to the logic model of the trial (Fig. 5) using the process measures below:
For the workers’ training component: number of training sessions held; number of participants in each training sessionFor improvement in KAP of workers: improvements in the proportions of workers reporting good knowledge, appropriate attitude and appropriate protective practices in the intervention compared to the control armFor the managers’ workshops: number and proportion of managers trained at each mill; proportion of mill managers using personal protective equipment (PPE) during visits to high-exposure areasChanges in KAP of managers: documented through a questionnaire and compared between the intervention and the control armFor administrative measures: number of meetings held by the “MultiTex” Committees; plans and policies developed at each mill as a consequence of the study; incorporation of training program in overall OHS plans of the millsFor PPE component: number of face-masks distributed on a daily basis and proportion of workers using face-masks at random visits conducted by the MultiTex Committee members

**Fig. 5 Fig5:**
[figure not shown]
MultiTex RCT– Logic model of the trial

We will use a checklist (Additional file 2) for evaluating the fidelity of our trial in line with the MRC guidelines for complex interventions, and the National Institutes of Health Behaviour Change Consortium’s (NIHBCC’s) guidelines on assessing fidelity in public health trials [27, 28]. This checklist considers aspects of fidelity in five specific domains: study design, training of providers, treatment delivery, treatment receipt, and treatment enactment. We will consider fidelity both at the mill and the worker level.

### Statistical analysis

Data will be entered through Epi Data and analyzed with STATA. Frequency counts will be derived for baseline socio-demographic variables and respiratory symptoms (categorical variables). Measures of central tendency and dispersion will be reported for continuous variables (cotton-dust levels and lung function indices). Correlations between the cotton-dust levels and lung function (FEV_1_, FVC and FEV_1_/FVC ratio) will be assessed through Pearson’s correlation coefficient.

Models based on generalized estimating equations (GEEs) will be developed to determine changes in the cotton-dust levels, frequency of respiratory symptoms, FEV_1_ (lung function indices) and respiratory sickness absenteeism. The changes in these outcome variables from baseline will be compared between the intervention and control groups. The GEE models will take into account the clustering by mills, as well as the correlation between repeated measures. Multicollinearity will be assessed between covariates and will be taken into account in the multivariable models.

We will analyze by intention to treat, and workers will be classified according to their assigned treatment group at the time of randomization. Sensitivity analyses will be performed to explore the potential impact of losses to follow-up.

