### Recruitment and randomization

In Pakistan, no official sampling frame of textile mills is available but several business and textile associations represent the country’s textile mills and from them we will acquire a list of industrial plants in Karachi. To be eligible, textile mills will need to: (1) be from the formal sector and registered with business associations and the Government Labor Department; (2) have either spinning or weaving sections, or both; (3) employ at least 50 eligible workers in their spinning and weaving sections; (4) have a workforce in which at least 75% of staff have been employed for 12 months or longer; (5) have a management willing to participate in the planning and implementation of the study and (6) have no plans to introduce major improvements over the next 2 years.

Eligible workers at each mill will be identified by the Human Resources Department. We will include male textile workers aged ≥ 18 years who are employed in the bale-opening, blowing, carding, spinning, twisting, winding, warping, weaving or waste recycling sections. In Pakistan, women very rarely work in these sections and we will not include them. Those who do not give consent will be excluded. We will also exclude workers from the wet-processing areas (dyeing or bleaching), stitching and packaging sections, as well as support or administrative staff. At each mill, personal air sampling will be done on five purposively selected workers (100–150 in all) representing the range of sections and jobs. For this purpose, the latter will be categorized into one of four groups: (1) helpers, cleaners and doffers; (2) machine operators; (3) jobbers and fitters and (4) masters, in-charge or supervisors.

We will purposively select 28 textile mills and assign them equally to the intervention or the control arm by stratified randomization. Stratification will be according to the total number of employees at the mill (≤ 250/> 250) and occupational health and safety measures in place at baseline (as assessed by a walk-through survey and categorized as good or poor). Within strata, allocation to intervention or control will be through random numbers generated at Imperial College London and shared with the research team in Pakistan. Blinding of mill staff will not be possible but we will “blind” the data collection team including the technicians measuring dust levels, and the laboratory personnel involved in weighing filters for gravimetric analysis.

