#### Spirometry and anthropometric measurements

We will use the ndd (EasyOne) spirometer to measure lung function, following established guidelines [26]. Forced expiratory volume in the first second (FEV_1_), forced vital capacity (FVC) and the FEV_1_/FVC ratio will be recorded. Pre- and post-bronchodilator spirometry will be conducted at least 1 h after the worker has started a shift (i.e., after he has been exposed to cotton dust that day). We will note the time of the day when spirometry is carried out, as well as the interval since start of the shift, and the number of consecutive days that have been worked leading up to the measurement. Every effort will be made to undertake spirometry at each follow-up on the same working day and during the same shift as at baseline. For a sub-sample of 100 randomly selected workers in the highly exposed job categories (helpers/cleaners and machine operators), pre- and post-shift spirometry will additionally be performed, to gauge cross-shift changes in lung function. We will record height in centimeters using a stadiometer, and weight in kilograms.

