#### Cotton-dust exposures

We will use IOM sampling heads with Casella Apex2 pumps for personal monitoring of dust exposures, measuring the inhalable fraction of particulate matter (PM < 100 μm) over an 8-h shift. Pre- and post-sampling airflow and sampling time will be recorded, as well as temperature and humidity readings. Each individual’s average PM exposure concentration will be calculated from the difference in filter weights and sampled air volume. Individual data will then be combined to derive mean exposures for combinations of job and section at each mill. Where possible, the same workers will be monitored at follow-up as at baseline, but those who cannot be re-contacted will be replaced by others with similar job tasks. Dust sampling will be done at all the textile mills across the intervention and control arms at baseline and will be repeated at 3, 12 and 18 months after intervention. In addition to personal sampling, area sampling will be carried out in the spinning and weaving sections of each mill using a Dylos DC 1700 particle counter to measure the average concentration of dust (particle size > 0.5 or > 0.25 μm) over an 8-h shift. The particle counters will be placed at fixed sites in the centres of work stations in the spinning and weaving sections, at approximately 1.5 m height, and away from the ventilation outlets or fans. Side-by-side gravimetric and Dylos measurements will be made for a small number of sites to provide a calibration factor for the Dylos particle concentration in relation to cotton dust.

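### The dust–lung function association rests on a plain Pearson correlation that ignores mill clustering, age and height; any test of it could be anti-conservative, depending on which dust values are used

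*Protocol article*

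**What the plan says.** The first paragraph of the Statistical analysis section covers frequency counts and summary measures. It ends with the one stated analysis of dust against lung function: "Correlations between the cotton-dust levels and lung function", for FEV1, FVC and FEV1/FVC, "will be assessed through Pearson’s correlation coefficient". No covariates, clustering, survey or exposure definition is attached to it.

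The next paragraph gives the models for dust, symptoms, FEV1 and respiratory sickness absence: "The GEE models will take into account the clustering by mills, as well as the correlation between repeated measures".

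Three other places matter for the data that would enter the correlation:

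- Cotton-dust exposures: "Individual data will then be combined to derive mean exposures for combinations of job and section at each mill". Recruitment and randomization has personal samplers worn by five workers at each mill.
- Measurements and their frequencies: "The surveys will include detailed interviews using a questionnaire, and spirometry for each worker". Surveys take place at baseline and at 3, 12 and 18 months.
- Spirometry and anthropometric measurements: "We will record height in centimeters using a stadiometer, and weight in kilograms".

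**The concern.** Workers sit within 28 mills, and both dust and lung function may be more alike within a mill than between mills. A standard test or confidence interval for Pearson's r assumes independent pairs. The authors handle this dependence in the outcome models but attach nothing to the correlation.

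Lung function is measured on every worker and personal dust on about five per mill. A correlation over all workers would therefore need group-mean dust values shared by many people in the same mill, which is the setting in which clustering matters most.

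FEV1 and FVC also depend on age and height. The job groups run from helpers to supervisors, so age in particular could differ between high-dust and low-dust jobs. A raw correlation would then mix that difference with any effect of dust.

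What is at stake is the reading of a secondary result. The trial is motivated by the idea that less dust means better lung function, and a dust–FEV1 correlation is likely to be taken as support for it. If r is distorted, or its precision overstated, that support is misjudged.

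**Working it through.** **The plan's own figures.** The article gives no figure for the correlation. Its nearest figures, in Statistical power, reproduce:

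- Variance inflation: 1 + (50 − 1) × 0.02 = 1.98.
- FEV1, difference 150 ml, SD 690 ml, two-sided 5%, power 80%: 333 per arm. 333 × 1.98 = 659.3, stated as 660.
- 28 × 61 = 1708 workers; 28 × 5 = 140 personally sampled workers.

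**Inputs for the check.** From the article: outcome ICC (ICC_y) 0.02, 28 mills, 61 workers per mill, 5 sampled per mill. Assumed, because the article does not give it: the mill-level ICC of the dust value attached to each worker (ICC_x), taken from 0 to 1. A value of 1 means every worker in a mill has the same dust value; 0 means dust does not cluster by mill.

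**Formula.** For two variables clustered in the same mills,

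design effect = 1 + (m − 1) × ICC_x × ICC_y,

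true error of a nominal 5% test = 2 × [1 − Φ(1.96 / √design effect)].

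The plan's inflation factor is the special case ICC_x = 1, m = 50.

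| Workers used | ICC_x | Design effect | SE understated by | True error | Simulated (28 mills, 6000 runs) |
|---|---|---|---|---|---|
| 1708 (m = 61) | 1 | 1 + 60 × 0.02 = 2.20 | 1.48 | 18.6% | 19.1% |
| 1708 | 0.5 | 1.60 | 1.26 | 12.1% | 11.6% |
| 1708 | 0.25 | 1.30 | 1.14 | 8.6% | 8.2% |
| 1708 | 0.1 | 1.12 | 1.06 | 6.4% | not run |
| 1708 | 0 | 1.00 | 1.00 | 5.0% | not run |
| 140 (m = 5) | 1 | 1 + 4 × 0.02 = 1.08 | 1.04 | 5.9% | 6.3% |
| 140 | 0.5 | 1.04 | 1.02 | 5.5% | 5.8% |

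At the ceiling, the effective number of workers is 1708 / 2.20 ≈ 776.

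**Size of r: age and height.** If dust has no effect once the covariate is held fixed, the spurious correlation is r(covariate, dust) × r(covariate, FEV1). With an assumed covariate–FEV1 correlation of 0.3 to 0.5 in absolute value:

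- covariate–dust correlation 0: spurious |r| is 0;
- 0.1: 0.1 × 0.3 = 0.03 to 0.1 × 0.5 = 0.05;
- 0.3: 0.3 × 0.3 = 0.09 to 0.3 × 0.5 = 0.15.

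**Size of r: choice of dust value.** A simulation with four job groups and five samples per mill started from an assumed individual-level r of −0.20. Replacing individual dust by job-group means gave about −0.15, −0.13 and −0.08 when 25%, 34% and 60% of the dust variance lay within groups. The variance shares are assumptions. The result shows that r depends on which dust value is used, and the article does not say which that is.

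**The case against.** The strongest reply is that the sentence is descriptive. It closes a paragraph of summaries and announces no test, p-value or confidence interval; inference begins in the next paragraph, with clustering handled. Exposure–response is not among the stated objectives, and all four items under Study outcomes compare the arms. This stands, and it limits the consequence.

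Several stronger readings are tempting, and the article does not support them:

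- **That the p-values are wrong.** None is planned in the text. The error rates above apply only if someone tests r.
- **That 19% is the expected error.** It needs one dust value per mill. Means by job and section vary within a mill, and the sampled workers are chosen to span sections and jobs, so 19% is a ceiling at the stated ICC.
- **That group means are certainly given to all workers.** The article derives these means but does not say that they enter the correlation. Using only the 140 sampled workers is equally compatible with the text, and the inflation is then negligible.
- **That the four surveys are pooled as if independent.** Nothing says so; the correlation could be computed at baseline or survey by survey.
- **That the size of r is shown to be wrong.** Clustering mainly affects precision. Distortion by age or height needs a relation with dust that the article does not quantify. It also does not say whether raw or percent-predicted values are used, a detail that may lie in the full protocol or analysis plan.

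What the reply does not remove is that the article names a method, rather than leaving one open. An unadjusted coefficient leaves age and height uncontrolled whichever workers are used, and with or without a p-value.

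**Conclusion.** The point holds as a secondary weakness in the choice of analysis. The only stated dust–lung function analysis is an unadjusted Pearson coefficient, in a section that already plans a more suitable model class.

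Its size is conditional. With group-mean dust for all 1708 workers, a nominal 5% test would run at between 5% and about 19%; with the 140 sampled workers, at no more than about 6%. Both rest on the protocol's ICC of 0.02, and the first also on an unknown dust ICC. The possible bias in r runs from none to about 0.15 in absolute value over the assumed covariate correlations. The randomized comparisons of dust, symptoms and FEV1 do not depend on this analysis.

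**What to change.** Estimate the association with the GEE already planned, or a mixed model: lung function (FEV1, FVC, FEV1/FVC) on dust, adjusted for age, height and survey, clustered on mill and with repeated measures within worker handled. Report the slope with a cluster-robust confidence interval. State which dust value each worker receives: his own sample, or the mean for his job and section at that mill. Keep Pearson's r, if wanted, only as a description without a p-value.

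Do not adjust for job group by default. Job helps define the exposure means, so adjustment would remove part of the dust contrast; use it at most as a sensitivity analysis.

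The cost is a sentence or two of analysis text. The model class is already planned, height is recorded, and age must be known to apply the eligibility criterion. The downside is that the association will look less precise.

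### Between-arm comparison of change from baseline, with no baseline adjustment named, is unbiased but gives up precision; for personal dust it may be noisier than the follow-up level alone

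*Protocol article*

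**What the plan says.** The Statistical analysis section plans GEE models for dust, symptoms, lung function and respiratory sickness absence, and names the contrast: "The changes in these outcome variables from baseline will be compared between the intervention and control groups". It adds: "The GEE models will take into account the clustering by mills, as well as the correlation between repeated measures". It mentions covariates in multivariable models without listing them. The baseline value of the outcome is not named as a covariate, and the arms are not constrained to a common baseline mean.

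The Study outcomes section words the primary outcomes in two ways. Symptoms and FEV1 are changes only: "changes from baseline in the prevalence of respiratory symptoms, in the intervention as compared with the control arm" and "changes in FEV_1_ from baseline to follow-up, in the intervention as compared with the control arm". Personal dust is both: "personal dust exposure levels (in mg/m^3^), and their change from baseline, in the intervention as compared with the control arm". Dust by mill section follows the same pattern.

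Personal dust is measured on five purposively chosen workers per mill (Recruitment and randomization). The Cotton-dust exposures section aims to re-measure the same men, but "those who cannot be re-contacted will be replaced by others with similar job tasks". It also combines individual results into means by job and section within each mill. The Discussion describes labour turnover as high. No replacement rate and no baseline to follow-up correlation are given.

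**The concern.** A change score subtracts the whole baseline value, whatever its predictive worth. Where baseline predicts follow-up only moderately, this adds baseline noise to the contrast. Regression on baseline subtracts only the part that predicts follow-up, so it is never less precise apart from the small cost of estimating the slope. Below a correlation of 0.5 the change score is noisier even than the follow-up value used alone.

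Personal dust is where this could matter most. It has the fewest measurements, each covers a single shift, and some men measured at follow-up may differ from those measured at baseline. Allowing for repeated-measures correlation in a GEE does not in general recover the loss. If baseline enters as one of the repeated outcomes with a free arm-by-time term, that term is still a difference in changes.

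**Working it through.** **The plan's own figures.** Two-sided 5%, 80% power, (1.960+0.842)² = 7.849:
- Dust: 2 × 7.849 × 2.5² / 0.65² = 232.2, so 233; × 1.98 = 461.
- FEV1: 2 × 7.849 × 690² / 150² = 332.2, so 333; × 1.98 = 659.3, so 660.
- Symptoms, 40% v 30%: 7.849 × (0.24+0.21) / 0.10² = 353.2, so 354; × 1.98 = 700.9, so 701.

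All reproduce. They are calculations for a single level, with no baseline correlation.

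**Relative variance**, with follow-up level alone = 1: change 2(1−r); baseline-adjusted 1−r²; ratio adjusted/change (1+r)/2. A sample sized for 80% power on levels has power Φ(2.80/√v − 1.96) under relative variance v. The values of r are assumptions.

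| r | change | adjusted | saving in variance | power, change | power, adjusted |
|---|---|---|---|---|---|
| 0.3 | 1.40 | 0.91 | 35% | 66% | 84% |
| 0.5 | 1.00 | 0.75 | 25% | 80% | 90% |
| 0.7 | 0.60 | 0.51 | 15% | 95% | 98% |
| 0.9 | 0.20 | 0.19 | 5% | >99% | >99% |

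**Personal dust at mill level.** Inputs from the protocol: m = 5 workers per mill, ICC 0.02. Assumed: within-worker correlation rw, share replaced f, a stable mill component, and a replacement who shares only that mill component with the man he replaces. Then

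R = [ICC + (1−f)(rw−ICC)/m] / [ICC + (1−ICC)/m].

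The denominator is 0.02 + 0.98/5 = 0.216. Example, rw = 0.5 and f = 0.25: (0.02 + 0.75 × 0.48/5)/0.216 = 0.092/0.216 = 0.426, so change is 2 × 0.574 = 1.15 and adjusted is 1 − 0.426² = 0.82.

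| rw | replaced | R | change | adjusted |
|---|---|---|---|---|
| 0.3 | 0% | 0.352 | 1.30 | 0.88 |
| 0.5 | 0% | 0.537 | 0.93 | 0.71 |
| 0.5 | 25% | 0.426 | 1.15 | 0.82 |
| 0.5 | 50% | 0.315 | 1.37 | 0.90 |
| 0.7 | 0% | 0.722 | 0.56 | 0.48 |
| 0.7 | 25% | 0.565 | 0.87 | 0.68 |
| 0.7 | 50% | 0.407 | 1.19 | 0.83 |
| any | 100% | 0.093 | 1.81 | 0.99 |

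The break-even R = 0.5 needs a numerator of 0.108, so 1−f = 0.44/(rw−0.02). Change becomes noisier than follow-up alone once more than about 8% are replaced at rw = 0.5 (0.44/0.48 = 0.917), or about 35% at rw = 0.7 (0.44/0.68 = 0.647). Below rw = 0.46 it is noisier with no replacement.

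A simulation with 28 mills of five workers agrees. At rw = 0.7 with half replaced it gives change 1.16 and adjusted 0.85; with all replaced, 1.83 and 1.03. The excess over 1 is the cost of estimating the slope from 28 mills.

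**Sensitivity to the ICC.** At an assumed ICC of 0.3 with stable mills and every worker replaced, R = 0.30/0.44 = 0.682, change is 0.64 and adjusted 0.54. Change then beats follow-up alone, and adjustment still beats change.

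**Dust power with the planned sampling.** With 14 × 5 = 70 workers per arm, design effect 1 + 4 × 0.02 = 1.08, difference 0.65 and SD 2.5, λ = 0.65/[2.5 √(2 × 1.08/70)] = 1.48. Follow-up alone has 32% power. Change v adjusted: 24% v 34% at R = 0.3; 32% v 40% at 0.5; 48% v 54% at 0.7; 91% v 92% at 0.9. These use normal quantiles; with 26 degrees of freedom the 32% is about 30%.

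**The case against.** The strongest reply is that the article names a contrast and does not specify an estimator. In a linear model, change adjusted for baseline gives the same arm effect as follow-up adjusted for baseline, so the wording does not exclude adjustment, and the covariate list may sit in an analysis plan that is not shown. This stands as a limit. The point is that the contrast as stated, with nothing added, is the less precise one; it is not that adjustment has been ruled out.

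Four stronger readings are tempting and are not supported:
- **That the change comparison is biased.** Under randomisation it is not. A chance baseline imbalance in one realised allocation is over-corrected by a change score, but averaged over allocations only precision is lost.
- **That replaced workers break the dust analysis.** They have no individual change, but the protocol already forms job-by-section means, replacements do similar work, and a model on levels uses every record.
- **That dust change scores are worse than ignoring baseline.** They can be. At rw = 0.7 with up to 25% replaced they are better, and similar job tasks may preserve more correlation than the formula allows. The protocol also lists the dust level itself as an outcome.
- **That the Statistical power section contradicts the analysis.** Sizing on single-level SDs is a common simplification, and it is conservative for change when r exceeds 0.5.

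The low dust power also comes mainly from having 70 sampled workers per arm against a calculated 461, which is a separate matter.

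**Conclusion.** The point holds as a loss of efficiency that costs almost nothing to avoid. For any r below 1 the adjusted comparison has the smaller variance, by (1+r)/2. The saving is worth having at moderate correlation (25% at r = 0.5) and minor at high correlation (5% at r = 0.9), which may be the case for FEV1. For personal dust, the protocol's own ICC and five workers per mill make it possible for the mill-mean correlation to fall below 0.5. Whether it does depends on the within-worker correlation, the replacement rate and the true mill ICC. The first two are not given, and the ICC of 0.02 is an assumption taken from other occupational trials. The figures therefore show a range and do not predict the loss in this trial.

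**What to change.** Define each primary effect as the 18-month between-arm difference adjusted for baseline:
- **FEV1:** the worker's own baseline FEV1 as covariate.
- **Symptoms:** the worker's baseline symptom status as covariate. Adjusting a logistic model gives a conditional odds ratio, so report a standardised (marginal) difference in prevalence. Under randomisation this targets the same quantity as the between-arm difference in change in prevalence given under Study outcomes.
- **Dust:** the mill or job-by-section baseline mean, which the Cotton-dust exposures section already derives, so that replacement workers contribute. With five samples per mill many job-by-section cells will hold one value or none, so name the mill mean as the fallback.

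An equivalent route is a repeated-measures model with the arms constrained to a common baseline mean. Report changes from baseline descriptively.

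The cost is wording in Study outcomes and Statistical analysis; no new data are needed. The statistical downside is about 3% in variance, against follow-up alone, from estimating the slope with 28 mills when baseline carries almost no information.
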